### Secondary outcome measures

Living conditions at final follow up are measured in percentage of pre-fracture situation.

• Self reported health-related quality of life is measured by the SF 12. [13]

• Standard radiological evaluation of hemiarthroplasty and cement positioning and adequate size of the hemiarthroplasty measured on plain AP and axial X-rays of the operated hip. Adequate AP positioning is defined as less than 10 degrees varus or valgus. Adequate axial positioning is defined as 0–15 degrees anteversion.

### Follow up

The primary follow up for each patient will be 1 year. The first postoperative assessment will be in a clinical setting as the patient is still in the hospital. Assessments at 6, 12 and 52 weeks postoperatively will be made in the outpatient clinic, unless the patient is not able to visit the outpatient clinic; in that case questionnaires are mailed to the patient (possibly through contact with a relative) to obtain as much data as possible.

### Determination of sample size

#### (a) Duration of surgery

It is expected that a cemented hemiarthroplasty on average will take 12 min longer than a non-cemented hemiarthroplasty. Taking into account an estimated standard deviation of 12 min, a 1-year mortality of 25% and 10% of patients being lost to follow up or providing insufficient data we need a minimum of 46 patients per group.

#### (b) Functional outcome

Only for patients who are admitted from their own homes or assisted living facilities, functional outcome is measured by the Timed-Up-and-Go (TUG) score and the Groningen Activity Restriction Scale, and mid-thigh pain a non-inferiority design is used. [10,14]

• TUG performed; Giving the fact that at discharge with a cut-off point of over 30 seconds is significantly associated with falls. Less than 24 seconds is considered good functioning and has hardly any chance to fall. 42 seconds is considered poor functioning with a considerable chance to fall. [14] About 30% of the patients have a poor score at discharge. About 70% of all patients are admitted from their own homes or assisted living facilities. If non-inferiority is considered for TUG, a worsening of score from 30 to 42 is considered clinically relevant, with a SD of 10 sec., giving 16 patients a group. Corrected for the percentage admitted from home or assisted living facility (70%) and the drop out of 35% gives 34 patients a group

• GARS: The GARS data for this group of patients are insufficient to make valid calculations of statistical power. While data for multiple sclerosis patients and healthy older patients are available, there are none for patients with a hip fracture. An estimate is made based on preliminary data from a prospective survey in progress. As soon as sufficient data from this survey are available a final power calculation for GARS will be done.

• Mid thigh pain

Rather varying figures about mid-tight pain are reported in literature. D'Lima [5] reported 40 vs. 3% whereas v/d Wal et al. [15] reported 20 vs. 12% in non-tight proximal fit prosthesis. Therefore the average values of these two studies are taken.

π1 = 30%, π 2 = 7.5%, π = (30%+7.5%)/2 = 18.75%

n_1 _= n_2 _≥ 21* (0,1875*(1-0,1875))/(0,225)^2 ^= 63.2.

If the 25% 1-year mortality combined with expected 10% lost-to follow-up (or missing values) is taken into account this number is raised by 35%, then a total of 86 patients a group is needed. [16]

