## Background

Patients with a hip fracture form a heterogeneous group with a high mortality rate, frequently troubled with multiple and severe co-morbidities. They are usually frail and elderly, with more than 30% aged ≥ 85 years. In European series, hip fracture patients have a 30-day mortality of >10%, and a 1-year mortality of 25–30%.[1] Despite the advances in surgical and anaesthetic techniques during the last 20 years there has been no decrease in mortality after surgical repair of hip fractures. [1]

The discussion about cemented or non-cemented hemiarthroplasty is similar to the discussion about cemented or cementless prostheses in primary hip arthroplasty. With respect to the latter, conflicting data are presented by the Swedish and Norwegian arthroplasty registers. [2,3] The general opinion is that cementless hip arthroplasties are more suitable for younger patients owing to the quality of their bone stock. In hemiarthroplasty for hip fracture surgery there are insufficient data from randomised trials to conclude on the superiority of either type of arthroplasty. Some authors found patients with cemented stems to have less pain and better mobility postoperatively than those with an non-cemented press fit.[4] Mid-thigh pain is frequently reported in primary cementless total hip arthroplasties. However, the reported incidence varies tremendously; D'Lima et al.[5] in a control-matched study reported 34%~vs.~3%, while Grübl et al.[6] in a non-controlled series reported only 3% for cementless primary total hip arthroplasties.

In cemented hemiarthroplasties polymethylmethacrylate bone cement is applied at the time of surgery, forming a solid bond between the prosthesis and the femoral bone; on the contrary, in cementless prosthesis the bonding between prosthesis and femur is dependent upon bony in-growth. Potential advantages of cementing are a less post-operative mid thigh pain, as the prosthesis is firmly fixed within the femur, and a reduced long-term revision rate from loosening of the prosthesis. Major side effects of cement are cardiac arrhythmias and cardio-respiratory collapse, which occasionally occur on application. These potentially fatal complications are caused either by embolism from marrow contents forced into the circulation or by a direct toxic effect of the cement. [7] Another major disadvantage of a cemented prosthesis is that revision arthroplasty will be more difficult.

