### Statistical analysis

#### Primary outcome measures

The differences in operation time, mid-thigh pain, complications and TUG test will be analyzed using a Student's t-test, setting the level of significance at *p *< 0.05.

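### Reference 5 is quoted with two different mid-thigh pain rates (34% and 40%), and the unexplained 40% feeds the largest sample size the plan calculates; if 34% is right, 100 per group falls short of the implied 90% power

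*Protocol article*

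**What the plan says.** The Background of the protocol article discusses mid-thigh pain after cementless hip replacement. It states that reference 5 "in a control-matched study reported 34%~vs.~3" (per cent).

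Under Determination of sample size, (b) Functional outcome, the mid-thigh pain item cites reference 5 again, and there it "reported 40 vs. 3% whereas" a second study "reported 20 vs. 12% in non-tight proximal fit prosthesis". The plan continues: "Therefore the average values of these two studies are taken". The planning rates follow as "π1 = 30%, π 2 = 7.5%, π = (30%+7.5%)/2 = 18.75" (per cent), and the number per group as "21* (0,1875*(1-0,1875))/(0,225)^2 ^= 63.2". Multiplying by 1.35, for 25% mortality plus 10% loss or missing data, brings this to 86 per group.

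The other calculated numbers are 46 per group for duration of surgery and 34 for the Timed-Up-and-Go test. The GARS calculation is deferred, and complications are said to need more patients than could be recruited. The planned size is 100 per group. No power is stated anywhere. The Statistical analysis section gives a significance level of 0.05 without saying whether it is one- or two-sided.

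**The concern.** The two statements share the reference, the outcome and the comparator rate of 3%. Only the rate in the cementless group differs, 34% against 40%. No other time point, subgroup or definition is offered to explain it. So one figure is wrong, or the two describe different things without saying so.

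The 40% is not a loose remark. The planning rate of 30% arises only from (40 + 20)/2, so it is a working input. It sits behind the largest per-group number calculated, for an outcome listed as primary, and no other calculated number comes near 100. At stake is whether 100 per group meets the requirement that the plan set for itself.

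**Working it through.** **Inputs.** Reference 5: 40% vs 3% (sample size section) or 34% vs 3% (Background). Second study: 20% vs 12%. Rule: simple mean of the two studies. Formula: n per group = 21 × p(1 − p)/d², where p is the mean of the two rates and d their difference. Attrition step: × 1.35. Planned enrolment: 100 per group.

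**The constant.** 2 × (1.960 + 1.282)² = 21.0, which corresponds to two-sided 5% and 90% power. The 90% is inferred from this.

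**The plan's own figure, with 40%**
- Rates: (40 + 20)/2 = 30%; (3 + 12)/2 = 7.5%; mean 18.75%; difference 22.5 points.
- n = 21 × 0.1875 × 0.8125 / 0.225² = 63.2.
- 63.2 × 1.35 = 85.3, so 86. Both stated numbers reproduce.

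**The same steps with 34%**
- Rates: (34 + 20)/2 = 27%; 7.5% as before; mean 17.25%; difference 19.5 points.
- n = 21 × 0.1725 × 0.8275 / 0.195² = 78.8, so 79 evaluable.
- 78.8 × 1.35 = 106.4, so 107 enrolled.

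If 35% of those enrolled are actually lost, the number to enrol is n/0.65 rather than 1.35n: 63.2/0.65 = 97.2, so 98, with 40%; and 78.8/0.65 = 121.3, so 122, with 34%.

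| Rate for reference 5 | Evaluable per group | Enrolled, × 1.35 | Enrolled, ÷ 0.65 | Planned |
|---|---|---|---|---|
| 40% | 63.2 (64) | 86 | 98 | 100 |
| 34% | 78.8 (79) | 107 | 122 | 100 |

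Under the plan's own attrition step, 100 per group is 14 above the requirement with 40% and 7 below it with 34%.

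**Sensitivity to the implied power.** At 80% power the constant is 2 × (1.960 + 0.842)² = 15.7. With 27% vs 7.5%, n = 15.7 × 0.1725 × 0.8275 / 0.195² = 58.9; × 1.35 = 79.6 and ÷ 0.65 = 90.7. Both are below 100.

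**Power with 100 enrolled per group** (two-sided 5%, normal approximation for two proportions). The plan's own step leaves 100/1.35 = 74 evaluable; a true 35% loss leaves 65. The first value in each pair uses the pooled variance throughout, as the plan's formula does. The second uses the unpooled variance under the alternative.

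| Rates compared | 74 evaluable | 65 evaluable |
|---|---|---|
| 30% vs 7.5% (from 40%) | 94% / 95% | 91% / 92% |
| 27% vs 7.5% (from 34%) | 88% / 89% | 84% / 85% |

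For example, with 27% vs 7.5% and 65 evaluable: 0.195 / √(2 × 0.1725 × 0.8275 / 65) − 1.960 = 0.98, which is 84%.

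**The case against.** The best reply is that the effect on the trial is small and conditional.

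- **Which figure is right is unknown.** If 40% is correct, the only defect is one number in the Background, and 63.2 and 86 stand. This is fair: the contradiction is certain, the shortfall is not.
- **The power target is inferred.** The shortfall against 100 needs the 90% implied by the constant 21. At 80% it disappears. This also stands, although 21 fits no other conventional choice as closely at two-sided 5%.
- **The loss is modest.** Under the plan's own attrition step, power would be about 89% against an implied 90%. Only the stricter reading, with 65 evaluable, brings it to 84–85%, which many would accept.
- **The inputs are rough anyway.** The plan concedes that published rates vary widely and takes the plain mean of two very different studies. A 3-point change in that mean is small beside the gap between them. True, but a rough input should still be the same number wherever the document prints it, above all when the calculated size depends on it.
- **The formula is not the planned analysis.** It compares two proportions for superiority. The outcome is a 4-point scale listed for a Student's t-test, and the section speaks of non-inferiority. The power figures here therefore describe the plan's sample size calculation and not the planned test.

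A reader might infer that the trial is underpowered or that the calculation contains an arithmetic error. The document supports neither. The arithmetic reproduces, and a shortfall exists only if 34% is right and 90% power was intended.

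**Conclusion.** The contradiction is established: one reference carries two rates, and the one used in the sample size is not the one given in the Background. This is an inconsistent input, and it should be fixed.

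Its size is conditional. If 40% is right, the sample size is unaffected. If 34% is right, the plan's own rule requires 79 evaluable and 107 enrolled per group (122 if 35% are actually lost) at the implied 90% power, against 100 planned. The power of the two-proportion comparison with 100 enrolled per group would then be about 89% with 74 evaluable, or 84–85% with 65 evaluable. With the 40% figure it is 91–92% at 65 evaluable.

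This assumes a two-sided 5% level, 90% power read from the constant 21, and the plan's simple averaging of the two studies. Mid-thigh pain is the largest requirement among those calculated; the GARS number is still open, and none is given for complications.

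**What to change.** Check reference 5 and use one figure in both the Background and the mid-thigh pain calculation. If the two numbers describe different time points, subgroups or definitions, say so and say why the chosen one applies.

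- **If 34% is right:** restate the planning rates as 27% and 7.5%, the mean as 17.25% and n as 79 evaluable per group. State the intended power, and give the power that 100 per group delivers for this comparison (about 89% with 74 evaluable, 84–85% with 65).
- **If 40% is right:** correct the Background only.

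The cost is one literature check and a few restated numbers. No extra patients and no design change are needed.

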## Discussion

In the treatment of displaced femoral neck fractures with hemiarthroplasty in elderly patients the use of bone cement is a controversial topic. A cemented hemiarthroplasty has been used in the majority of cases in most countries, but the non-cemented prosthesis is gaining popularity. Parker et al. [1] concluded that there is only limited evidence from randomised studies that cementing prosthesis in place may reduce the amount of post-operative pain and may lead to improved mobility. Furthermore no study has adequately addressed long-term outcome measures concerning this topic.

Cementing has potential physiologically adverse side effects. The major side effects cardiac arrhythmias and cardio-respiratory collapse, which occasionally occur upon application; these potentially fatal complications are caused either by embolism from marrow contents forced into the circulation or by a direct toxic effect of the cement. [7] Transesophageal echocardiography could be used to monitor emboli during surgery, but logistics prevent this in our centres, as most patients are operated outside regular working hours. Nevertheless, Pitto et al. [17] have already shown severe embolic events and intraoperative pulmonary impairment during fixation of the cemented femoral component in total hip arthroplasty, while fixation without cement clearly demonstrated a low risk of embolism. Clark et al. [18] found a transient but significant reduction in cardiac output and stroke volume for those receiving cement.

In non-cemented prostheses, bone quality is of importance; this is generally poor in elderly patients. LaPorte et al. [19] stated two relative contraindications for non-cemented total hip prosthesis: interference with bone in-growth and inability to achieve a congruent fit; both of these preclude establishment of rigid initial stability.

The purpose of this study is to compare treatment for displaced femoral neck fracture by cemented versus non-cemented hemiarthroplasty. We hypothesise that, relative to cemented hemiarthroplasty, non-cemented hemiarthroplasty will result in at least the same technical-functional outcome and complication rate, with a shorter operation time. The results of this study will be presented as soon as they become available.

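### Mid-thigh pain is labelled non-inferiority, but its sample size is presented as a test to detect 30% vs 7.5%, with no margin, so the size supports no non-inferiority conclusion at any stated margin

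*Protocol article*

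**What the plan says.** All references are to the protocol article.

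- **Design label.** The opening sentence of Determination of sample size (b) Functional outcome says that for "mid-thigh pain a non-inferiority design is used".
- **Planning rates.** Under Mid thigh pain in the same section, one cited study "reported 40 vs. 3% whereas" the other "reported 20 vs. 12% in non-tight proximal fit prosthesis". The plan continues: "Therefore the average values of these two studies are taken". The result is "π1 = 30%, π 2 = 7.5%, π = (30%+7.5%)/2 = 18.75" percent.
- **Calculation.** The number per group is "21* (0,1875*(1-0,1875))/(0,225)^2 ^= 63.2", raised by 35% for death and loss to follow-up to 86.
- **Margin.** None is given for mid-thigh pain. For TUG, the same section names a worsening from 30 to 42 seconds as clinically relevant.
- **Analysis.** Statistical analysis, Primary outcome measures, tests differences in mid-thigh pain (with operation time, complications and TUG) by Student's t-test at p < 0.05.
- **Hypothesis.** The Discussion expects that "non-cemented hemiarthroplasty will result in at least the same technical-functional outcome and complication rate", and the Abstract says the same.
- **Direction.** The Background reports mid-thigh pain as frequent with cementless total hip stems and lists less of it as a potential advantage of cementing.

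**The concern.** A non-inferiority design needs a margin, an assumed true difference (usually zero) and a rule that compares a confidence limit with the margin. For mid-thigh pain the plan has the label and none of these. It has two unequal expected rates and a test of difference, which answer another question: whether the arms differ.

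The risk lies in the reading of a null result. Under the label, a non-significant t-test could be reported as showing that the non-cemented stem is no worse for pain. Failure to find a difference does not show that, and with no margin there is nothing to show it against. Mid-thigh pain is a primary outcome, and its 86 per group is the largest figure calculated (46 for duration of surgery, 34 for TUG; GARS left pending, complications judged unachievable). It is therefore the evident, though unstated, basis for 100 per group.

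The planning rates also point away from the hypothesis. Read with the Background, they assume more pain in the non-cemented arm. That sits badly with an at-least-the-same claim if mid-thigh pain counts as a functional outcome, as the sample-size heading suggests.

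**Working it through.** **1. Reproduce the plan's figure.** Inputs, all from section (b): 30% = (40 + 20)/2; 7.5% = (3 + 12)/2; mean 18.75%; difference 22.5 points.

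n = 21 × 0.1875 × 0.8125 / 0.225² = 63.19, which is the stated 63.2. Then 63.19 × 1.35 = 85.3, rounded up to 86. Both figures reproduce.

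**2. Identify the test.** 2 × (1.96 + 1.2816)² = 21.01. The constant 21 is therefore two-sided 5% (equally, one-sided 2.5%) with 90% power. With the two rates entered as expected values, this is the pooled-variance formula for detecting 30% vs 7.5%.

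**3. Power to detect 30% vs 7.5% at 64 evaluable per group.** Pooled SE = √(2 × 0.1875 × 0.8125 / 64) = 0.0690. Power = Φ(0.225/0.0690 − 1.96) = 0.90. With the unpooled variance under the alternative it is 0.91. The planned 100 per group, less 35%, leaves 65.

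**4. If the home or assisted-living restriction applies.** The sentence that carries the non-inferiority label opens by restricting measurement to patients admitted from home or assisted living, put at about 70%. The TUG calculation corrects for this and the mid-thigh pain calculation does not. If it applies, 100 × 0.65 × 0.70 = 45.5, about 45 per group:

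- pooled SE = √(0.3046875/45) = 0.0823
- unpooled SE = √((0.21 + 0.069375)/45) = 0.0788
- power = Φ((0.225 − 1.96 × 0.0823)/0.0788) = 0.79

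**5. What the size would give under non-inferiority.** The documents state no margin, so the margins here are assumptions, at one-sided 2.5% and equal true rates p. Power = Φ(m / √(2p(1−p)/n) − 1.96), with n = 65:

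| Margin m | p = 7.5% | p = 18.75% |
|---|---|---|
| 10 points | 58% | 31% |
| 15 points | 90% | 59% |
| 22.5 points | 99.8% | 91% |

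The power depends heavily on two quantities, the margin (not stated) and the common rate (not stated). With 45 evaluable, the 15-point figure at 7.5% falls to 77%.

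**6. Counter-check.** A non-inferiority formula with both true rates at 18.75% and a 22.5-point margin gives 2 × 0.1875 × 0.8125 × (1.96 + 1.2816)² / 0.225² = 63.24, the same number. The arithmetic alone cannot exclude that reading; the text must decide it.

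**The case against.** **22.5 points could be the margin.** Step 6 shows that the number fits. But the plan presents 30% and 7.5% as averages of reported rates, never as a common rate with a margin, and the analysis compares nothing with 22.5 points. As a margin it would accept a rise from 7.5% to 30%, the very gap taken from the literature. The objection stands only this far: the formula by itself does not prove the difference reading.

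**The label may be a slip in a badly constructed sentence.** Sizing to detect more pain without cement agrees with the Background. The hypothesis speaks of technical-functional outcome and complications, while the Abstract and Primary outcome measures list mid-thigh pain separately from functional outcome. So a flat contradiction with the hypothesis is not established; the tension is conditional. The label still conflicts with the calculation and with the test.

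**The arms are not labelled.** Section (b) does not say which arm has 30%. That it is the non-cemented arm is inferred from the Background. The mismatch between label and calculation does not depend on it.

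**Stronger readings that do not hold.** A reader might infer that this sample size could never support non-inferiority. Step 5 shows otherwise: at a common rate of 7.5%, 65 per group gives about 90% power for a 15-point margin. A reader might also count it as a defect that non-inferiority would almost never be concluded if the truth were 30% vs 7.5%. At a 22.5-point margin that chance is 2.5%, the type I error by construction, and a sound test should fail when the new arm is much worse.

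**Margins belong in the analysis plan.** The point does not rest on an omission. The article prints a full calculation and a test that do not match its own label.

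**Conclusion.** The concern holds in this form: for mid-thigh pain the label is non-inferiority, while the calculation as presented and the planned test are for a difference. The stated size (63.2 evaluable, 86 per group) therefore supports no non-inferiority conclusion at any stated margin, and a non-significant t-test would not supply one.

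The size itself is adequate for the question it was calculated for: about 90% power for 30% vs 7.5% at 64 evaluable per group, or about 79% if only patients from home or assisted living count. This rests on the plan's own rates and 35% loss. The direction of the assumed difference is an inference from the Background, and that this calculation set the total of 200 is an inference from its being the largest.

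**What to change.** **Preferred.**

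- Remove the non-inferiority label for mid-thigh pain.
- State that about 64 evaluable per group gives about 90% power, two-sided 5%, to detect 30% vs 7.5%, and say which arm is expected to have which rate.
- Report the difference with its 95% confidence interval.
- State that a non-significant result is not evidence of non-inferiority.
- Say whether the home or assisted-living restriction applies to mid-thigh pain. If it does, restate the power as about 79% with about 45 evaluable per group.

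**If non-inferiority is kept.** Prespecify and justify an absolute margin below 22.5 points, compare the confidence limit with it, and restate the power together with the assumed common rate. The 15-point figures under the working are for illustration only; nothing in the documents supports that margin.

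**Cost.** The preferred fix needs protocol wording and a restated power figure, with no extra patients unless the restriction applies and 90% power is still wanted. Keeping non-inferiority may need more patients: at 90% power a 10-point margin requires 146 evaluable per group at a common rate of 7.5% and 321 at 18.75%.

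### The mid-thigh pain sample size is inflated by multiplying by 1.35 instead of dividing by 0.65, so 86 per group should be 98 (94 if losses are sequential); follow-up losses are also charged to operation time

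*Protocol article*

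**What the plan says.** All of this stands in the protocol article under Determination of sample size.

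- **Mid-thigh pain, in (b) Functional outcome.** The assumed rates are "π1 = 30%, π 2 = 7.5%, π = (30%+7.5%)/2 = 18.75"%. The evaluable number per group is "21* (0,1875*(1-0,1875))/(0,225)^2 ^= 63.2". Attrition enters as "If the 25% 1-year mortality combined with expected 10% lost-to follow-up (or missing values) is taken into account", and the result is "this number is raised by 35%, then a total of 86 patients a group is needed".
- **Timed-Up-and-Go (TUG), also in (b).** The basis is "a worsening of score from 30 to 42 is considered clinically relevant, with a SD of 10 sec., giving 16 patients a group". Then: "Corrected for the percentage admitted from home or assisted living facility (70%) and the drop out of 35% gives 34 patients a group".
- **Duration of surgery, in (a).** A 12 min difference and an SD of 12 min are combined with the same 25% mortality and 10% loss or insufficient data, and the conclusion is "we need a minimum of 46 patients per group". No formula or power is shown. Primary outcome measures defines this outcome as skin-to-skin time in minutes.

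Section (c) then sets enrolment at 100 per group, 200 in total.

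**The concern.** The 35% is a share of the patients enrolled, so 65% of them remain evaluable. Multiplying the evaluable number by 1.35 does not undo a 35% loss, because 35% of the inflated number is lost, which is more than was added. The error sits in the largest of the three calculated sample sizes, the one closest to the planned 100 per group. A reader who compares 86 with 100 would think that pain is covered with room to spare.

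Two related faults stand beside it. The TUG calculation uses the same attrition but not the same arithmetic. Operation time is charged with deaths and losses during the following year, which cannot remove a measurement already taken in theatre.

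**Working it through.** **Assumptions.** The protocol gives a significance level of 0.05 without saying one- or two-sided, and no power. The multiplier 21 equals 2 × (1.96 + 1.2816)² = 21.01, so I take two-sided 0.05 and 90% power throughout.

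**Mid-thigh pain**

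1. Evaluable number: 21 × 0.1875 × 0.8125 / 0.225² = 63.19, so 64. This agrees with the protocol's 63.2.
2. The protocol's inflation: 63.19 × 1.35 = 85.3, so 86. The stated figure is reproduced.
3. Correct inflation, losses added to 35%: 63.19 / 0.65 = 97.2, so **98**.
4. Correct inflation, losses sequential (evaluable fraction 0.75 × 0.90 = 0.675): 63.19 / 0.675 = 93.6, so **94**.
5. What 86 would deliver: 86 × 0.65 = 55.9 evaluable. Power by the protocol's own formula is Φ(√(n × 0.225² / (2 × 0.1875 × 0.8125)) − 1.96). With n = 55.9 this is Φ(3.048 − 1.96) = 0.862. With sequential losses, n = 58.05 and power is 0.874.

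The planned 100 per group, by the same formula:

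| Scenario | Evaluable per group | Power | Enrolment needed per group |
|---|---|---|---|
| 35% loss | 100 × 0.65 = 65 | 0.908 | 98 |
| 30% mortality plus 10% loss | 100 × 0.60 = 60 | 0.884 | 63.19 / 0.60 = 105.3, so 106 |
| 35% loss, pain limited to the 70% from home | 100 × 0.70 × 0.65 = 45.5 | 0.785 | 63.19 / 0.455 = 138.9, so 139 |

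The 30% is the upper end of the one-year mortality range given in the Background. The last row applies only under one reading of the opening sentence of (b).

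**TUG**

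1. A t-test with difference 12, SD 10 and 90% power needs 15.62, so 16. This agrees with the protocol.
2. Division, sequential losses: 16 / (0.70 × 0.675) = 33.9, so 34. The stated figure is reproduced.
3. Division, flat 35%, from the unrounded number: 15.62 / (0.70 × 0.65) = 34.3. From 16 it is 35.2, so 36.
4. The multiplication used for pain: 16 / 0.70 × 1.35 = 30.9, so 31. This does not give 34.

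The TUG figure therefore follows from division, and the pain figure from multiplication.

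**Duration of surgery**

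1. A t-test with difference 12, SD 12 and 90% power needs 22.02, so **23** per group with no attrition.
2. With attrition at 90% power: 23 × 1.35 = 31.05, so 32; 23 / 0.675 = 34.1, so 35; 23 / 0.65 = 35.4, so 36.
3. Dividing by 0.65 gives 27 at 80% power and 42 at 95% power.

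None of these is 46. With 46 evaluable per group the power would be 99.7%.

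**The case against.** The strongest reply is that nobody plans to enrol 86. The protocol sets 100 per group, which under its own 35% loss leaves 65 evaluable against 64 needed. Even at 30% mortality the power is about 88%. This stands: the design survives, and the error lies in an intermediate figure. It is still a stated sample size that does not follow from its inputs.

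Second, 98 is not the only correct answer. The protocol does not say whether the 10% loss is taken from all patients or from survivors, so 94 is equally defensible. This also stands, but no reading of the losses brings the figure down to 86.

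Several stronger readings are tempting, and the document does not support them:

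- *All three sample sizes are wrong through attrition.* The TUG figure of 34 comes out of correct division. Taken with a flat 35% loss, 34 enrolled leave 15.5 evaluable and 89.7% power, so the gap to 36 is a matter of rounding.
- *The origin of 46 is known.* It lies close to 21 / (0.65 × 0.70) = 46.15, which would mean that the home-admission factor was used, and it also equals 2 × 23, which would mean a total printed as a per-group number. The protocol shows no steps, so neither can be confirmed.
- *The protocol claims a reserve of 14 per group.* It makes no such claim; the reader would have to infer it from 100 − 86.
- *Pain needs 139 per group.* The opening sentence of (b) is garbled and can be read as limiting pain to home admissions. However, Primary outcome measures lists pain apart from functional outcome, and the 70% correction is applied only to TUG. This is an ambiguity to resolve, not an established shortfall.

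**Conclusion.** The point holds for two of the three calculations. The pain figure is an arithmetic error: 86 should be 98, or 94 with sequential losses, a shortfall of 8 to 12 per group. At 86 the power would be about 86 to 87% rather than 90%. For operation time the attrition factor does not belong, about 23 per group suffice, and 46 does not follow from the stated inputs, though it errs on the safe side. The TUG figure is sound; it only shows that attrition is treated inconsistently.

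The consequence is limited. With 100 per group, pain has about 91% power under the protocol's assumptions, but the margin over 98 is only 2 patients per group, and at 30% mortality 100 falls below the 106 needed for 90% power. These results rest on two-sided 0.05 and 90% power inferred from the multiplier 21, and on the protocol's own rates, SDs and losses. The operation-time result also assumes that skin-to-skin time is recorded for essentially every patient operated on.

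**What to change.** 1. Restate mid-thigh pain as 98 per group, or as 94 with a statement that the losses are sequential.
2. Use one attrition method, division by the expected evaluable fraction, for every outcome followed over the year. If the losses are declared sequential, the TUG figure of 34 can stay as it is.
3. Restate duration of surgery as about 23 per group without an attrition factor, with its power and sidedness.
4. State whether the restriction to patients admitted from home or assisted living covers mid-thigh pain.
5. Keep 200 patients and state the power they deliver for pain: about 91% with 65 evaluable per group, about 88% if one-year mortality is 30%, and, if pain is limited to home admissions, about 79%.

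The cost is a few corrected sentences in the sample size section. No extra patients, visits or data are needed.
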